### Study procedure

In the intervention arm of the trial, the BEACON Caresystem is activated by the research team and subsequent ventilator management determined by system advice, applied to the ventilator by the clinical team, as illustrated in figure 2 and described below. In the control arm, the BEACON Caresystem is activated in a mode in which system advice is disabled, but data are still collected by the BEACON Caresystem. The ventilator management in this arm is determined by standard care.

**Figure 2 F2:**
[figure not shown]
Flow chart of BEACON Caresystem intervention arm. ABG, arterial blood gas; ALPE, automatic lung parameter estimator; CRF, clinical research form; SBT, spontaneous breathing trial.

### Intervention arm

Figure 2 illustrates the protocol flow in the intervention arm. At any time during the protocol, adverse events are addressed immediately, with a serious event resulting in exclusion from the study (illustrated as B in figure 2). Minor events are documented and the patient returned to the main protocol flow (illustrated at point A, at the top of figure 2). During intervention, the BEACON Caresystem can provide a number of different forms of advice to the user which require action. These are illustrated at the top of figure 2, and are described in turn below.

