#### Spontaneous breathing trial (SBT)

During weaning from mechanical ventilation, the BEACON Caresystem monitors the levels of Pressure Support (PS) and Positive End Expiratory Pressure (PEEP). When these levels are reduced to values below clinical guideline thresholds,^21^ the BEACON Caresystem automatically monitors variables evaluating spontaneous breathing criteria. If these remain within limits and for a duration determined by international guidelines,^21^ the system prompts the user to assess the appropriateness of extubation and provides a checklist to help. The primary function of the BEACON Caresystem with regards weaning is to reduce levels of support where possible; it does not suggest an active SBT or extubation. As such, the decision to extubate is according to standard clinical practice for both arms of the study, meaning that at any time the clinical team can perform an active SBT or extubate the patient without confirmation from the system. Reintubation is documented by the research team and the participant enters a standard care pathway, which involves the deactivation of the BEACON Caresystem. The participant is then followed up until the end of the protocol (figure 1).

The protocol ends with transfer or discharge from ICU or death (figure 1).

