## Safety, ethics and dissemination

### Adverse events

All adverse events will be monitored and documented until the end of study. Adverse events are reported to the trial sponsor according to their standard operating procedure for further investigation. As patients are critically ill, it is expected that unrelated adverse events will occur as part of hospital stay. Adverse events are therefore only defined in relation to changes in mechanical ventilation, for patients allocated to either the control or intervention arms.

Serious adverse events are defined as:Death, suspected to be caused directly by the settings of mechanical ventilation.Adverse events include the following events suspected to be caused directly by the settings of mechanical ventilation:Pneumothorax.Self-extubation.Hypoxaemia (SpO_2_ <90%; PaO_2_ <8.00 kPa).Alkalaemia (pH >7.5).Acidaemia (pH <7.2).

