### Ethical approval and consent

Study approval was obtained from the regional ethics committee of the HRA, REC reference: 17/LO/0887. IRAS reference: 226 610. The majority of the trial population lack the capacity to consent. Therefore, participant information sheets and advice are requested from a third party acting as a consultee; in most cases, this person will be a personal consultee, who is someone who knows the person lacking capacity and is able to advise the researcher about that person’s wishes and feelings in relation to the project and whether they should join the research. However, where the personal consultee is not available, the researcher may nominate a professional person to assist in determining the participation of a person who lacks capacity. A nominated professional consultee will be appointed by the researcher to provide advice regarding the patient’s suitability to participation in the research. In the event that a personal consultee is identified after the nominated professional consultee advice has been obtained, the above process for personal consultee declaration will be followed. A patient information sheet will be distributed immediately following the patient being identified as eligible for the study. If a surviving patient regains capacity, they will be approached by the research team to obtain their consent to continue in the study. If the patient refuses consent or withdraws, the intervention will be stopped but the regular/expected medical care will still be provided. Without consent, no additional information about the patient will be collected for the purposes of the study. However, to maintain integrity of the randomised trial, all information collected up to that time will still be used and analysed as part of the study.

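### The intervention-arm flow excludes patients from the study after a serious event, without saying what this means for follow-up or analysis, and it does not fit the protocol's own definition of serious

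*Protocol article*

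**What the plan says.** The rule stands in the protocol article, section Intervention arm, which opens by tying itself to one arm: "Figure 2 illustrates the protocol flow in the intervention arm". Adverse events are to be addressed immediately, "with a serious event resulting in exclusion from the study". By contrast, "Minor events are documented and the patient returned to the main protocol flow".

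Other sections bear on it:

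- **Adverse events** lists a single serious adverse event: "Death, suspected to be caused directly by the settings of mechanical ventilation". The definitions cover both arms. All adverse events are to be documented until the end of the study and reported to the sponsor.
- **Spontaneous breathing trial (SBT)** ends the protocol at ICU transfer, ICU discharge or death. After reintubation, "the participant enters a standard care pathway, which involves the deactivation of the BEACON Caresystem", and the next sentence keeps the participant in follow-up to the end of the protocol.
- **System malfunction** moves the patient to standard care and does not speak of exclusion.
- **Ethical approval and consent** covers refusal or withdrawal: no further data are collected, but "all information collected up to that time will still be used and analysed as part of the study".
- **Study procedure** says of the control arm that the device is "activated in a mode in which system advice is disabled, but data are still collected", and adds: "The ventilator management in this arm is determined by standard care". It gives no exclusion rule for serious events.

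**The concern.** Exclusion from the study is an instruction that sites can follow literally. It takes effect after randomisation and is triggered by an outcome. The trigger is also partly a judgement, because the event must be suspected to come from the ventilator settings, and the clinical team making that judgement applies the device's advice and so knows the allocation.

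ICU mortality and ventilation-related adverse events are both secondary outcomes. If patients with an attributable death leave follow-up or the analysis set, the arms are no longer compared as randomised on the outcomes where a harm from ventilator settings would show. An analysis plan can restore patients to the analysis set, but it cannot recover outcomes that sites stopped collecting.

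**Working it through.** **1. The passages side by side**

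| Departure | Section | What happens to the patient or data |
|---|---|---|
| Reintubation | Spontaneous breathing trial (SBT) | Device off, follow-up to protocol end |
| Malfunction | System malfunction | Standard care until corrected |
| Refusal or withdrawal | Ethical approval and consent | Data collected so far are analysed |
| Minor event | Intervention arm | Documented, patient continues |
| Serious event | Intervention arm | Exclusion from the study; nothing on follow-up or data |

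Only the last row lacks a clause that keeps the patient or the data. Since the sole serious event defined is an attributable death, and death ends the protocol anyway, three readings are possible:

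- (a) The rule is redundant.
- (b) It takes attributable deaths out of the study's results.
- (c) Serious event here is wider than the Adverse events definition, and the sections conflict.

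**2. The plan's own figure**

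Inputs from Statistical considerations: 137 per arm, difference 2 days, SD 7.0 in controls, SD 30% lower (4.9) with the device, alpha 0.05 (taken as two-sided), power 0.80. With the average SD of 5.95:

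n = 2 × (1.960 + 0.842)² × 5.95² / 2² ≈ 139 per arm, close to the stated 137.

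With separate SDs of 7.0 and 4.9, power at 137 per arm is 78.2%. Excluding 7 intervention patients lowers it to 77.5%, and excluding 14 to 76.7%. Lost power is not the issue.

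**3. ICU mortality under reading (b)**

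The documents give neither a mortality rate nor a serious event rate. Assume the same d baseline deaths in each arm of 137, plus x attributable deaths in the intervention arm only. The intervention rate is (d + x)/137 with everyone counted and d/(137 − x) after exclusion.

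| Assumed baseline, d/137 | x | Everyone counted | After exclusion |
|---|---|---|---|
| 14/137 = 10.2% | 3 | 17/137 = 12.4% | 14/134 = 10.4% |
| 14/137 = 10.2% | 7 | 21/137 = 15.3% | 14/130 = 10.8% |
| 27/137 = 19.7% | 3 | 30/137 = 21.9% | 27/134 = 20.1% |
| 27/137 = 19.7% | 7 | 34/137 = 24.8% | 27/130 = 20.8% |
| 41/137 = 29.9% | 3 | 44/137 = 32.1% | 41/134 = 30.6% |
| 41/137 = 29.9% | 7 | 48/137 = 35.0% | 41/130 = 31.5% |

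With x = 7 the excess over control is 7/137 = 5.1 points when everyone is counted. After exclusion it shrinks to 0.6, 1.1 and 1.6 points at the three baselines.

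**4. Primary outcome under reading (c) only**

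The primary outcome runs to successful extubation, so a patient who dies before that has no duration as defined, and dropping that patient does not change the mean. If serious event also covers survivors, assume no true effect (mean 7.2, SD 7.0 in both arms) and x excluded patients ventilated e days longer than average:

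bias = x·e/(137 − x), SE = 7.0 × √(1/137 + 1/(137 − x)).

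- x = 1, e = 3: bias 3/136 = 0.02 days, two-sided type I error 5.0%.
- x = 3, e = 7: bias 21/134 = 0.16 days, type I error 5.4%.
- x = 7, e = 7: bias 49/130 = 0.38 days, SE 0.857, type I error 7.2%.
- x = 14, e = 7: bias 98/123 = 0.80 days, type I error 15.0%.

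The bias favours the device if the excluded patients would have been ventilated longer than average, which is itself an assumption.

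**The case against.** The strongest reply is that the sentence describes bedside workflow, not analysis. It does not say that data are discarded, and analysis populations are commonly set in an analysis plan, which is not shown. That stands as far as it goes: a reader might infer that intention-to-treat is definitely broken, and the article does not say so. The rule is nonetheless stated, not merely left open, and its plain wording points away from continued follow-up.

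Other stronger readings also fail:

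- **One arm only.** This rests on where the sentence stands. The event definitions cover both arms, and figures 1 and 2 are not visible. One can say only that the text shown gives controls no such rule.
- **The device's harms are deleted.** Adverse events must be documented to the end of the study and reported to the sponsor, and an independent committee looks at safety data after 80 patients. The threat is to the between-arm comparison, not to the safety record.
- **The primary outcome is biased in favour of the device.** This needs a serious event wider than death. If an analysis gave deaths a duration, the direction would depend on when they occurred.
- **The withdrawal provision is contradicted.** It governs consent, not serious events. It shows a different practice and, if anything, suggests that the authors meant to keep data.
- **Reintubation is handled in the same faulty way.** It is not: follow-up explicitly continues.

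**Conclusion.** The concern holds as a defect of wording with a real statistical risk. As written, the rule is a post-randomisation exclusion triggered by an outcome, and it does not agree with the definition of serious adverse event or with the end-of-protocol rule. If sites or analysts apply it literally, attributable deaths drop out of the comparison of ICU mortality and ventilation-related events, and most of any excess would be hidden.

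The size cannot be determined, because the documents give no event rate. The mortality figures rest on assumed baselines of 10% to 30%, on 3 or 7 attributable deaths in the intervention arm alone, and on removal from the analysis. With one or two such events the effect would be small. Effects on the primary outcome arise only under the wider meaning of serious event.

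**What to change.** Replace the exclusion wording under Intervention arm with a statement on data, for example: *every randomised patient, in either arm, is followed for outcomes to the end of the protocol and analysed in the allocated arm, and serious events and deaths are counted in the outcomes; refusal or withdrawal of consent is handled as described under Ethical approval and consent.*

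Then reconcile the term serious event across Intervention arm, Adverse events and the end-of-protocol rule in the SBT section, so that a site can tell which events are meant. If an analysis plan exists, its analysis population should say the same.

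Nothing is proposed here on device use or clinical care after an event; those passages are for the sponsor to settle. The cost is a wording change and a note to sites, with no extra patients.

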#### Arterial blood gas (ABG)/automatic lung parameter estimator (ALPE)

In situations where mathematical model simulations cannot accurately describe continuous measurements, that is, SpO_2_, fraction of end-tidal CO_2_ (FetCO_2_), or in support ventilator modes respiratory frequency or tidal volume, then retuning of the models is required. In this situation, the BEACON Caresystem requests either an ABG, or a short procedure varying FiO_2_ to assess pulmonary gas exchange (ALPE), as described and evaluated previously,^16–20^ and briefly described in the online supplementary material.

10.1136/bmjopen-2020-042145.supp1Supplementary data

#### Ventilator

Advice on changing ventilator settings. New advice is generated only when the system regards current settings as not appropriate. Duration between advice therefore varies, however, for PEEP and changes in volume or pressure 10–20 min is the minimum period between advice.

#### Bounds

The BEACON Caresystem allows for bounds to be set for the limits of advice on ventilator settings. If advice is available which is outside these bounds, the protocol dictates that the bedside nurse consults with the clinician on duty.

#### Mode/sedation

If the BEACON Caresystem detects substantial spontaneous breathing during control ventilator modes, advice is provided to consider changing to support mode. Additionally, if pH falls below a defined value in support mode, advice is provided to consider changing to control mode or modifying sedation. In either situation, the protocol dictates that the bedside nurse consults with the clinician on duty.

#### Spontaneous breathing trial (SBT)

During weaning from mechanical ventilation, the BEACON Caresystem monitors the levels of Pressure Support (PS) and Positive End Expiratory Pressure (PEEP). When these levels are reduced to values below clinical guideline thresholds,^21^ the BEACON Caresystem automatically monitors variables evaluating spontaneous breathing criteria. If these remain within limits and for a duration determined by international guidelines,^21^ the system prompts the user to assess the appropriateness of extubation and provides a checklist to help. The primary function of the BEACON Caresystem with regards weaning is to reduce levels of support where possible; it does not suggest an active SBT or extubation. As such, the decision to extubate is according to standard clinical practice for both arms of the study, meaning that at any time the clinical team can perform an active SBT or extubate the patient without confirmation from the system. Reintubation is documented by the research team and the participant enters a standard care pathway, which involves the deactivation of the BEACON Caresystem. The participant is then followed up until the end of the protocol (figure 1).

The protocol ends with transfer or discharge from ICU or death (figure 1).

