### Primary and secondary outcomes

The primary outcomes include:

Duration of mechanical ventilation to successful extubation defined as the time from the start of mechanical ventilation, defined as either the time of intubation in the ICU, or the time of admission to the ICU following previous intubation for surgery, and until successful extubation, with successful extubation defined as ≥48 hours of unassisted spontaneous breathing after extubation.

Unassisted spontaneous breathing is defined here to include supplementary oxygen and support with high-flow nasal catheters. Patients with non-invasive mask ventilation are considered to be assisted.

The secondary objectives of the trial are to compare the following variables in the standard care group and BEACON Caresystem group:

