Duration of mechanical ventilation to successful extubation following randomisation defined as the time from randomisation and until successful extubation, with successful extubation defined as ≥48 hours of unassisted spontaneous breathing after extubation.Time from control mode to support mode defined as the time following randomisation, from initiation of control modes of ventilation and until initiation of support modes of ventilation.Time from support mode to successful extubation defined as the time following randomisation, from initiation of support modes of ventilation and until successful extubation.Number of changes in ventilator settings per day defined as the daily registered number of changes to ventilator settings from randomisation until successful extubation.Time to first SBT defined as the time from randomisation to the first performed SBT.Time to first successful SBT defined as the time from randomisation to the first successful SBT.Time to first extubation defined as the time from randomisation to the first extubation attempt.Time to first disconnection from mechanical ventilation defined as the time from randomisation to the point at which mechanical ventilation is first discontinued.Percentage of time in control mode ventilation defined as the time from randomisation which is spent in controlled modes of mechanical ventilation in per cent of duration of mechanical ventilation.Percentage of time in support mode ventilation defined as the time from randomisation which is spent in support modes of mechanical ventilation in per cent of duration of mechanical ventilation.Use of sedatives defined as the cumulative use of sedative drugs from randomisation until successful extubation.Use of neuromuscular blockading agents defined as the cumulative use of neuromuscular blockading agents from randomisation until successful extubation.Number of intubation free days defined as the number of days without intubation from randomisation until successful extubation.Number of reintubations defined as the number of reintubations following extubation from randomisation until successful extubation.Number of tracheostomies defined as the number of patients having tracheostomy performed from randomisation until successful extubation or protocol end.Number of patients on prolonged mechanical ventilation defined as the number of patients on mechanical ventilation ongoing for more than 21 days after the start of mechanical ventilation.Number and types of adverse events related to mechanical ventilation defined as the incidence of adverse events directly related to mechanical ventilation.ICU mortality defined as the mortality from randomisation and until death or ICU discharge.Length of stay defined as the duration of ICU admission from the start of mechanical ventilation and until death or ICU discharge.Mobilisation times defined as the time from randomisation until (1) first mobilisation, for example, sitting on the edge of the bed, standing up and marching on the spot and (2) regaining independency, for example, able to drink/eat or comb hair.Daily patient physiological blood gas status defined as daily ABG values of SaO_2_, PaO_2_, PaCO_2_, pH from randomisation until successful extubation.Daily average physiological status defined as daily averages of measured values of oxygenation (SpO_2_), end-tidal CO_2_ fraction (EtCO_2_), ventilation (respiratory rate, tidal volume, anatomical dead space), pulmonary mechanics (airway pressure, respiratory system compliance) and ventilator settings as measured routinely at the bedside.

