
### Statistical considerations

Sample size was determined by a power analysis of duration of mechanical ventilation. Extrapolation of the 2016 ICU admission data from two London-based NHS hospitals provided a sample size of 548 patients over an 18-month period. In these patients, mean total duration of mechanical ventilation measured in days was 7.2, with an SD of 7.0 days. A study population of 137 patients in each randomisation group would allow detection of a 2 day or 30% improvement in the duration of mechanical ventilation in the BEACON Caresystem group assuming a similar improvement in SD, with an α level of 0.05 and power of 0.8. A 2 days or 30% reduction in duration of mechanical ventilation is similar to that used previously.^6^

Primary and secondary outcomes will be measured across the protocol duration and comparison made by independent samples t-test, or appropriate non-parametric testing if not normally distributed. Complementary analysis will be performed using Kaplan-Meier curves.

The study is not sufficiently powered to allow subgroup analysis for the groups specified in the randomisation strategy.

An independent data safety monitoring committee will be established as part of the study, with this committee responsible for defining stopping criteria. Safety data will be looked at after the first 80 patients have been recruited, with an interim analysis performed following 50% recruitment.

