## Discussion

This paper presents the study protocol of single-blinded multicentre randomised control trial evaluating management of mechanical ventilation as directed by the BEACON Caresystem compared with that of standard care in the general intensive care setting. To test the hypothesis that following advice from the BEACON Caresystem will reduce time to successful extubation, patients are randomised to care including advice from the system, or standard care. In addition, as secondary outcomes, the study will investigate whether application of the advice changes the time spent in control ventilation modes, the number of changes made to the ventilator, the use of medication such as sedative or neuromuscular blocking agents, the changes in clinical procedures such as reintubation or tracheostomy and clinical and physiological status of the patient. Although not powered to detect differences between groups, it will also investigate the length of stay at the ICU and patient mortality.

This study is the next step in evaluation of the advice of the BEACON Caresystem. A large number of studies have been performed validating the physiological models included in the system, as summarised in,^9^ and studies of short duration have been performed evaluating the physiological response to application of advice.^14 15^ This use of the system over the whole duration of ICU stay allows for assessment of more meaningful clinical outcomes, relating to the time spent on mechanical ventilation. In addition, the study includes only patients intubated for a minimum of 24 hours, meaning that short-term postoperative patients who may have rather uncomplicated intubation periods are not included.

The study includes limitations. The study was powered on duration of mechanical ventilation rather than duration to successful ventilation, this being the historical data available during study design. The study is not powered to detect changes in mortality, and does not follow-up on the patients after transfer from the ICU. In the context of this study, successful extubation is defined as the lack of need for non-invasive ventilator support for 48 hours after extubation, rather than successful rehabilitation of the patient subsequent to their ICU stay.

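### Success needs 48 hours of observation after extubation, but follow-up stops at ICU exit, so the primary outcome is unconfirmed for patients who leave earlier

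*Protocol article*

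**What the plan says.** All references are to the protocol article.

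- **Endpoint.** Under Primary and secondary outcomes, the primary outcome is the time from the start of mechanical ventilation to successful extubation, "with successful extubation defined as ≥48 hours of unassisted spontaneous breathing after extubation". High-flow nasal support counts as unassisted, but "Patients with non-invasive mask ventilation are considered to be assisted".
- **End of follow-up.** The section on the spontaneous breathing trial closes with "The protocol ends with transfer or discharge from ICU or death". For a reintubated patient the same section says "The participant is then followed up until the end of the protocol", which is the same stopping point.
- **Measurement window.** Statistical considerations: "Primary and secondary outcomes will be measured across the protocol duration". The comparison is by t-test or a non-parametric test, with Kaplan-Meier curves as a complement.
- **After the ICU.** The Discussion lists as a limitation that the study "does not follow-up on the patients after transfer from the ICU".
- **A related outcome.** Tracheostomies are counted in patients "having tracheostomy performed from randomisation until successful extubation or protocol end". This wording allows the protocol to end before successful extubation. The primary outcome has no such clause.

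**The concern.** The endpoint is confirmed by a fixed 48-hour window after extubation, whereas follow-up is tied to where the patient is. Nothing in the article makes the first fit inside the second. Two groups fall into the gap:

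1. Patients extubated in the ICU who leave it within 48 hours. Reintubation or mask ventilation elsewhere during the rest of the window would not be seen.
2. Patients transferred out while still ventilated. Their duration has no observed end.

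For the first group the analyst can drop the patient, assume success or assume failure. Dropping loses data. Assuming success misses support restarted after ICU exit. Assuming failure misclassifies patients who did breathe unassisted. The secondary outcomes that run to successful extubation, such as the duration from randomisation, inherit the problem. An analysis plan can choose a rule for incomplete outcomes, but it cannot recover data that were never collected.

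**Working it through.** **Step 1: the conflict.** This needs no arithmetic. Let t be the hours from extubation to ICU exit.

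| Situation at ICU exit | Observed | Can the definition be applied? |
|---|---|---|
| Extubated, t ≥ 48 | the full window | yes |
| Extubated, t < 48 | t hours; 48 − t hours unseen | extubation time known, success unconfirmed |
| Still ventilated, transferred | no extubation | no end time |

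No sentence in the article extends observation for the second and third rows. None says that leaving the ICU counts as success, failure or censoring.

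**Step 2: the plan's own power.** Inputs from Statistical considerations:
- comparison SD 7.0 days around a mean of 7.2 days
- improvement of 2 days or 30%, with a similar improvement in SD
- α 0.05 and power 0.8
- 137 patients per group

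Assumptions: two-sided test; intervention SD 0.7 × 7.0 = 4.9 days. The 30% reading gives δ = 0.30 × 7.2 = 2.16 days.

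Standard error = √[(7.0² + 4.9²)/n] = √(73.01/137) = 0.730 days.

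- δ = 2.0: 2.0/0.730 = 2.74. Normal-approximation power = Φ(2.74 − 1.96) = 0.782; t-based power 0.779.
- δ = 2.16: 2.16/0.730 = 2.96. Normal-approximation power = Φ(2.96 − 1.96) = 0.841; t-based power 0.838.

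The number per group for 80% power is 73.01 × 7.849/δ², which gives 144 for 2.0 days and 123 for 2.16 days. The stated 137 lies between them, so the stated power of 0.8 is broadly reproduced.

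**Step 3: illustration of loss.** The article does not give the share of unconfirmed outcomes. I assume a share f, equal in both arms, and assume that every such outcome is unusable. Then n = 137(1 − f) per group. Power is t-based.

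| f (assumed) | Unusable of 274 | n per group | Power, 2.0 days | Power, 2.16 days |
|---|---|---|---|---|
| 0% | 0 | 137 | 0.78 | 0.84 |
| 10% | about 27 | 123.3 | 0.74 | 0.80 |
| 20% | about 55 | 109.6 | 0.68 | 0.75 |
| 30% | about 82 | 95.9 | 0.63 | 0.69 |

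Example for f = 20%: standard error = √(73.01/109.6) = 0.816; 2.0/0.816 = 2.45, which gives 0.68.

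The fall is about 4, 9 to 10, or 15 percentage points on either reading of the effect. The table shows lost precision only; it says nothing about bias.

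**The case against.** **The article may condense a fuller procedure.** It says that the protocol ends at ICU exit, which is not quite the same as saying that all data collection ends there. Figure 1, cited for the end point, is not shown, and a 48-hour ward check is a detail an article could omit. Routine hospital records could also hold the answer. This has some force: the outcome is unconfirmed under the follow-up described, not unknowable. It does not remove the conflict, because the measurement window and the Discussion both point to the same stopping place.

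**The limitation is disclosed.** Only in part. The Discussion mentions the lack of post-ICU follow-up together with mortality, and does not connect it with the 48-hour window.

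**The size is hypothetical.** This stands. The shares have no anchor in the article, and the power loss assumes that every such outcome is deleted, which the article does not say. With the 30% effect, power is still about 0.80 after a 10% loss. The complementary Kaplan-Meier analysis could also retain censored patients.

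**A stronger reading is tempting.** A reader might infer that early leavers are the fastest recoveries, so that losing them hides the device's benefit. The documents do not support this. The endpoint depends on the time from the start of ventilation to extubation; the gap depends on the time from extubation to ICU exit. A patient ventilated for 20 days may leave 40 hours after extubation, and one ventilated for 2 days may stay a week. Patients transferred while ventilated are not fast recoveries at all. Bias is possible if the timing of ICU exit differs by arm, since the clinical team applies the advice and treats both arms, but its direction is unknown.

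**Conclusion.** The conflict is real and stands in the current text: the endpoint needs 48 hours of observation after extubation, and the stated follow-up does not guarantee it. Success is unconfirmed for patients who leave the ICU inside that window, and the end time is missing for those transferred while ventilated.

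The size cannot be derived from the article. The power figures are illustrative: they rest on assumed shares of 10% to 30%, complete deletion of those outcomes, a two-sided test and an intervention SD of 4.9 days. No direction of bias is claimed. The point merits a change because the remedy is cheap and must be in place while outcome data are being collected.

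**What to change.** Amend the end-of-protocol statement for outcome ascertainment only; patient care is unaffected.

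- **Patients extubated before leaving the ICU.** For those alive and not withdrawn, record reintubation and mask ventilation until death or 48 hours after extubation, whichever comes first, even if the patient has left the ICU. Use ward or receiving-hospital records.
- **Patients transferred while still ventilated.** Obtain the extubation date from the receiving unit where possible. Otherwise keep them in the Kaplan-Meier analysis as censored at transfer, and do not drop them. State that the planned t-test cannot use a censored duration, and that censoring at transfer assumes transfer is unrelated to the remaining time on ventilation.

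The cost is one amendment and a small record check per early leaver, with somewhat more effort where another hospital must be contacted. The check must respect the rule under Ethical approval and consent that no further information is collected once a patient refuses consent or withdraws. With complete ascertainment, the planned 274 participants need no change on this account.
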